**Demographic and clinical data**						
Eligibility	✓					
Centre	✓					
Date of birth	✓					
Gender	✓					
Ethnicity	✓					
Marital status/dependents	✓					
Living arrangements	✓					
Usual place of residence	✓					
Educational level	✓					
Group membership	✓			✓		
Height and weight	✓					
Employment status	✓					
Benefits/pensions status	✓					
Start of current illness	✓					
Start of disabling episode	✓					
Comorbid medical conditions	✓	✓	✓	✓	✓	
Medications and therapies	✓	✓	✓	✓	✓	
Oxford criteria	✓			✓	✓	
CDC criteria/CDC symptoms	✓			✓	✓	
London criteria	✓			✓	✓	
Fibromyalgia	✓			✓	✓	
Past medical history	✓					
Preferred intervention group	✓					
Adverse events		✓	✓	✓	✓	
**Therapist data**^ **c** ^						
Primary qualification	✓					
Years of experience	✓					
Years of relevant experience	✓					
Employment grade	✓					
**Doctor data**^ **c** ^						
Discipline	✓					
Employment grade	✓					

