**Trial periods (recruitment and follow-up)** Recruitment was initially intended to be ongoing for 36 months, with three centres recruiting during the first 12 months, six centres recruiting during the subsequent 24 months, and three centres recruiting at twice the annual rate during the last 12 months. Due to a funding extension, a seventh centre (Bristol) was added and recruitment was ongoing for 45 months.

SSMC is ongoing over 52 weeks; therapy in APT, CBT and GET is ongoing for the first 23 weeks with one booster session between 36 and 52 weeks. Participants are followed up at 12, 24, and 52 weeks.

##### 

**Research visit window definitions** Screening data are collected prior to baseline visit 1; baseline data are collected prior to randomisation. Baseline visit 2 is at least one week after baseline visit 1. Baseline CFQ and SF-36PF should be collected within one month prior to randomisation. Follow-up data should be collected within one week of the expected date where possible. Week 52 follow-up data can be collected at any time after week 52 with no specified upper time limit other than the end of 52 week data collection for the trial (31 January 2010).

When research visits fall outside of the guidance window, they will be analysed according to the most appropriate time point. Specifically, planned visits taking place up to 18 weeks will be used for the 12-week data, while the closest planned visit will be used for the 24- and 52-week data. If a planned visit data is missing, previous unscheduled visit data can be used instead.

Visit windows will be summarised to indicate whether their distribution is similar across interventions; the use of unscheduled visits will also be summarised.

Where variation in visit times is large, or the average visit time differs across interventions, time will be fitted as a continuous instead of a categorical variable. This decision will be made by a consensus judgement of the authors.

#### **
*General considerations*
**

##### 

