##### **Efficacy outcomes**

##### 

**Definition of outcome measures (including trial periods)** All secondary efficacy outcomes are defined separately at weeks 12, 24 and 52 unless specified otherwise (see Baseline and Outcome Measures). The PACE Scoring Protocol outlines in detail the process for calculating scores from questionnaire items and variables from case report forms. Participant-, therapist- and SSMC doctor-rated CGI are defined as ordinal variables with three categories. Participant satisfaction is defined as an ordinal variable with seven categories. The anxiety and depression subscale scores of the HADS, the Walking Test, and the total score of the Work and Social Adjustment scale are all continuous variables. However, the distribution of these is not pre-specified with the possibility that some or all may be skewed and the Walking Test may be bimodal. The number of CDC symptoms is a count variable and CDC Symptoms (1) and (8) are binary variables.

##### 

**Descriptive statistics for outcome measures** The distributions of all secondary efficacy outcomes will be presented in histograms (continuous/count) or bar charts (ordinal/binary) both overall and by intervention at each assessment point. A single table will be produced including summary statistics for all secondary efficacy outcomes by intervention and assessment point. Numbers (and percentages) or means (and standard deviations, minimums and maximums) or medians (and inter-quartile ranges, minimum and maximums) will be presented as appropriate. Summary statistics will be further plotted using line graphs for each outcome across time by intervention. The anticipated profiles have not been specified in advance. Potential variability in secondary efficacy outcomes between therapists and between doctors will be investigated using an approach similar to that outlined for the primary outcomes.

##### 

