**Primary analysis (including method of analysis)** The primary analyses addressing secondary objective (3) will involve the secondary efficacy outcomes and will be based on the intention-to-treat principle. Participant will be included as a random intercept (investigating adding a random slope on time), time (investigating the possibility of linearising this effect across 12, 24 and 52 weeks) and the associated baseline variable as fixed effects and centre, CDC criteria, London criteria, and Current Depressive Disorder as fixed indicator variables. Participant-rated CGI and the participant satisfaction will be analysed using mixed-effects ordinal logistic regressions. The anxiety and depression subscale scores of the HADS, number of CDC symptoms, the Jenkins sleep scale total score, the Walking Test, and the total score of the Work and Social Adjustment scale will be analysed using mixed-effects linear regressions, unless there is evidence to suggest that these outcomes are skewed/bimodal, in which case transformation and bootstrapping will be investigated. CDC Symptoms (1) and (8) will be analysed using mixed-effects logistic regressions. The intervention and time-by-intervention contrasts fitted for the primary outcomes will be extracted for each secondary efficacy outcome as outlined in the analyses of the primary outcomes.

##### 

**Baseline adjustment** The same as that outlined for the primary outcomes

##### 

**Model assumptions checks** The following will be checked as described for the primary analysis of the primary outcomes

1. Independence of residuals

2. Distribution of residuals

3. Equal variance of residuals

4. Distribution of random effects (as appropriate)

5. Absence of an intervention-by-centre interaction

6. Extreme outliers and points with high leverage

##### 

**Other analyses supporting the primary analysis** Sensitivity analyses investigating the robustness of the conclusions of the primary analyses of the secondary efficacy outcomes will be less extensive than those described for the primary outcomes unless concern is raised by those carried out for the primary outcomes.

##### 

**Safety outcomes** These analyses will be based on the safety sample (see Trial Samples).

##### 

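### CDC Symptoms (1) and (8) have one scheduled follow-up, so the planned participant-random-intercept logistic model has almost no information on its variance and can inflate their odds ratios

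*SAP article*

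**What the plan says.** Three parts of the SAP bear on this.

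- **Schedule.** In Table 2 (Timing of research assessments), the row "CDC criteria/CDC symptoms" is ticked at baseline, week 52 and discontinuation of therapy. Weeks 12 and 24 are blank.
- **Definition.** Under Efficacy outcomes, "All secondary efficacy outcomes are defined separately at weeks 12, 24 and 52 unless specified otherwise", with a cross-reference to Baseline and outcome measures, where Table 2 stands. The same paragraph gives the data types: "The number of CDC symptoms is a count variable and CDC Symptoms (1) and (8) are binary variables".
- **Model.** The primary analysis of secondary efficacy outcomes sets one template. It begins "Participant will be included as a random intercept (investigating adding a random slope on time" and adds time across 12, 24 and 52 weeks, the baseline value and the stratification factors as fixed effects. It then says "CDC Symptoms (1) and (8) will be analysed using mixed-effects logistic regressions", and that "The intervention and time-by-intervention contrasts fitted for the primary outcomes will be extracted for each secondary efficacy outcome". No exception is made for an outcome with a single follow-up.

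Two further rules matter. Research visit window definitions says: "If a planned visit data is missing, previous unscheduled visit data can be used instead". Method for handling other clustering effects adds a population-average (GEE) model for binary outcomes, alongside the random-effects model.

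**The concern.** Among the listed efficacy outcomes, CDC symptoms are the only ones with a single scheduled follow-up. The walking test and participant satisfaction have two, and the rest have three. The template was written for repeated measures and carried over unchanged.

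In a logistic model this matters more than in a linear one. The odds ratio from a random-intercept logistic model is conditional on the participant effect, and its size depends on the SD of that effect. With one yes/no value per person, the data say next to nothing about that SD. The reported odds ratio could then reflect wherever the fitting routine stopped. The SAP's multiplicity section bases interpretation mainly on the size and precision of effects, using point estimates and unadjusted 95% confidence intervals, so an arbitrary scale would be read as an effect size.

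**Working it through.** The SAP gives no figure for this model, so there is none to reproduce. The check is whether the model can be estimated from the data that the schedule yields.

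**Step 1: records per participant.** Baseline is a covariate. Week 52 is the only scheduled outcome. A discontinuation visit may only stand in for a missing planned visit, so it adds no second record. Each participant contributes one binary outcome.

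**Step 2: time terms.** If every record belongs to week 52, a time effect coded over 12, 24 and 52 weeks duplicates the intercept, and the time-by-intervention terms duplicate the arm terms. Neither can be estimated. If actual visit dates were used instead, as the SAP allows in some circumstances, a time coefficient could be computed. It would describe how late participants were seen, not change over follow-up.

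**Step 3: arms only.** With one record each, the model is P(Y=1) = ∫ expit(xβ + σz) φ(z) dz, where σ is the random-intercept SD. Four arm parameters fit four observed proportions exactly, whatever σ is, so the likelihood is flat. In one simulated data set of 641 participants (the number randomised) in four arms, the log-likelihood was −420.564641 at σ = 0, 1, 2, 3 and 5. One arm's odds ratio was 0.364, 0.296, 0.192, 0.113 and 0.036 respectively.

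**Step 4: planned covariates.** Adding baseline symptom, CDC criteria, London criteria, depressive disorder and six centres leaves only the shape of the link to inform σ. Event rates and covariate effects are assumptions, because the SAP gives none (for example, symptom present at baseline in 80%, and true odds ratios of 1, 0.6 and 0.5 against the reference arm). In the same data set:

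| σ | Log-likelihood | Odds ratio, arm A | Odds ratio, arm B | Log odds ratio relative to σ = 0, arm A |
|---|---|---|---|---|
| 0 | −388.954 | 0.525 | 0.343 | 1 |
| 1 | −388.924 | 0.466 | 0.280 | ln 0.466 / ln 0.525 = 1.19 |
| 2 | −388.906 | 0.357 | 0.180 | 1.60 |
| 3 | −388.900 | 0.259 | 0.105 | 2.10 |
| 5 | −388.902 | 0.127 | 0.032 | 3.20 |

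The usual approximation, √(1 + 0.346σ²), gives 1.16, 1.54, 2.03 and 3.11 at σ = 1, 2, 3 and 5. A separate run with 641 participants and the planned covariates gave 1.16, 1.54, 2.01 and 3.05.

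**Step 5: how often it bites.** In 200 data sets generated with true σ = 0, σ was chosen by likelihood from a grid of 0 to 5:

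- Twice the log-likelihood range across the grid had median 0.16 and 95th percentile 0.61, against the usual 3.84. The separate run gave 0.28 and 0.88.
- The best value was 0 in 49.5% of data sets and 4 or 5 in 45.5%. Because 5 is the edge of the grid, a free fit could go further.
- The log odds ratio relative to ordinary logistic regression had median ratio 1.05 and 90th percentile 3.26.

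**Step 6: effect on the test.** In 60 further data sets (580 participants, assumed event rates), the likelihood-ratio statistic for one treatment contrast averaged 5.37 with σ fixed at 0 and 5.39 with σ fixed at 5. It fell on different sides of 3.84 in none of the 60.

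**The case against.** The defence is substantial, and much of it stands.

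- **The plan has a companion estimate.** With one record per participant, the GEE reduces to ordinary logistic regression with robust standard errors, which is the right estimate. But it is fitted as well as the mixed model. A reader who saw two odds ratios could take the gap for the ordinary difference between subject-specific and population-average effects.
- **A sensible analyst would drop the random intercept.** The SAP ties it to repeated measurements, lets outcome timing vary, permits sensible statistical practice and foresees alternatives if a model fails to converge. This makes harm less likely. The timing clause does not alter the model, however, and a fit with an inflated odds ratio need not fail to converge.
- **The items are marginal.** CDC Symptoms (1) and (8) appear in neither the list of efficacy outcomes nor Table 3, both of which name only the number of symptoms. No multiplicity-adjusted claim rests on them.

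A reader might infer more than the documents support, in three ways:

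- *That the symptom count is biased too.* It gets a linear model. There, one record per person only confounds the intercept variance with the residual variance and leaves the fixed-effect estimates unchanged.
- *That inflation is certain, or that false positives follow.* About half of the simulated fits matched ordinary logistic regression, and the likelihood-ratio test hardly moved.
- *That the variance is strictly unidentifiable in the planned model.* That is exact for arms only. With covariates it is weakly identified, though not usefully.

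**Conclusion.** The point holds for the two binary items. The SAP names a model that its own assessment schedule cannot support. Its time and time-by-intervention terms cannot be estimated as planned, and its odds ratio rests on a variance about which the data are nearly silent. The log odds ratio is about 1.2, 1.5 to 1.6 and 2.0 to 2.1 times the ordinary one at SD 1, 2 and 3, for almost no change in likelihood.

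The scaling with SD is a general property of the logistic-normal model. The share of fits that inflate depends on the assumed event rates and covariate effects, and on a grid that ended at SD 5. Likelihood-ratio significance was checked only in the 60 simulated data sets. The sign of the effect stayed the same at every SD in the illustrative data set.

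This is a minor correction. It concerns the scale of the odds ratios for two secondary items and leaves the co-primary analyses untouched.

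**What to change.** Add one sentence to the primary analysis of secondary efficacy outcomes: CDC Symptoms (1) and (8) will each be analysed at week 52 by single-level logistic regression on intervention, baseline value, centre, CDC criteria, London criteria and depressive disorder, with no participant random effect and no time or time-by-intervention terms. This replaces the mixed model for these items, so the companion GEE is no longer needed for them.

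For the number of CDC symptoms, the redundant random intercept and time terms can be dropped from the linear model in the same sentence. That is tidying and corrects no bias.

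The change needs no new data and makes the analysis simpler.

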##### **Descriptive statistics for outcome measures**

##### 

**Serious deterioration** Serious deterioration will be tabulated both overall and by its four components at week 52 by randomised intervention. Absolute risk difference tests will be performed between serious deterioration (yes or no) and randomised intervention.

##### 

**Adverse events** Adverse events will be tabulated separately by type (non-serious adverse events, serious adverse events, serious adverse reactions and suspected unexpected serious adverse reactions), by time (weeks 0 to 12, weeks 12 to 26, weeks 26 to 52, and overall weeks 0 to 52), and by randomised intervention. Each table will include denominators showing how many participants were in the trial at each time point by randomised intervention. The numerator will indicate the number of affected participants, and an event rate will be provided indicating the events per unit of person time so as to capture events with recurrences.

The frequency of non-serious adverse events (non-serious adverse events and non-serious adverse reactions) per participant will be tabulated by randomised intervention.

All serious adverse events will be described individually: stating randomised intervention, participant identification number, centre, sex and age, investigator's reported term, preferred term, date of onset according to the date of the randomization, duration, number of SSMC sessions, number of therapist sessions (if applicable), action taken regarding the study intervention administration, use of a corrective treatment, outcome, relationship to the study intervention in the PACE clinician’s opinion and expectedness. Where the independent scrutineers have disagreed with the PACE clinician’s opinion, the scrutineers’ views only will be reported.

Deaths will be reported as described for a serious adverse event.

All adverse events leading to withdrawal (which constitute significant adverse events) will be summarised by randomised intervention, and whether the participant withdrew from the whole trial or intervention only.

##### **Discontinuation and withdrawals from intervention**

Discontinuation and withdrawals from intervention will be listed by intervention, participant identification number, centre, who made decision for withdrawal, whether the participant withdrew from intervention or trial, the reason for withdrawal, and interval post-randomisation (in days). Reasons for discontinuation and withdrawal from intervention will be tabulated by time (week 0 to week 12, week 12 to week 26, week 26 to week 52 and week 0 to week 52), randomised intervention and reason for withdrawal.

More detailed descriptions of adverse events will be published separately.

##### 

**Primary analysis (including method of analysis)** All serious adverse events (SAEs, SARs and SUSARs combined) will be tabulated in relation to the intervention. Any doubling in harms observed between interventions will be highlighted. The percentages of participants with SAEs, SARs and SUSARS, and the three combined, as well as number of non-serious AE and percentage of participants with one or more non-serious AEs, will be reported by intervention group, including differences between groups with 95% CIs.

##### **Health economics outcomes**

**Definition of outcome measures (including trial periods) Service use and lost employment** Comprehensive data are being collected on all health, social care and other relevant services used by individual study members using a tailored version of the Client Service Receipt Inventory (CSRI). The CSRI is used at baseline and at 24- and 52-week follow-up each time covering resource use for the previous 6 months. The CSRI covers the following broad categories of information.

• Living situation/accommodation

• Education, employment and income (including benefits)

• Time off work (measured in days) and time unemployed (or retired due to illness) summing the relevant cost period (−24 to 0 weeks, 0 to 24 weeks 0 to 52 weeks)

• Use of health and social care resources

##### 

**Cost calculation** The costs of each resource item will be calculated using best available unit cost estimates [75]. The cost of APT, GET and CBT will be estimated using information on the core resource inputs involved in delivering the interventions, and estimating country-specific costs for those inputs. Costs will be calculated using data on the number of intervention sessions received by each participant.

Lost employment costs for those in employment will be calculated by combining time off work with daily earnings. For those unemployed/retired due to ill health lost employment costs will be calculated by combining this period of time with average age and gender specific earnings.

The variables derived from the CSRI will be: (i) use (yes/no) of each service, (ii) number of service contacts/days in hospital, (iii) cost of each service, (iv) in employment (yes/no), (v) days not worked, and (vi) whether benefits received (each benefit - yes/no).

##### 

**Quality adjusted life year measurement** The EQ-5D consists of five domains (mobility, self-care, usual activities, pain/discomfort, and anxiety/depression). Each of these will receive a score of 1, 2 or 3 corresponding to no problems, moderate problems and major problems. Utility scores will be attached to each health state based on these scores (a table of utility values [76] has been produced by the Centre for Health Economics, University of York). These utility scores will be used to generate QALY gains over the follow-up period.

##### 

**Descriptive statistics for outcome measures** Data will be reported on the number and percentage of participants using each service in the CSRI by intervention, at baseline and 24 and 52 week follow-up. The mean and standard deviation number of service contacts for using services will also be reported as well as the mean and standard deviation costs for all participants. The number and percentage of participants with a score of 1, 2 or 3 for each EQ-5D domain will be reported.

##### **Primary analysis (including method of analysis)**

**Cost comparisons** Regression analysis will be used to compare service costs and total costs between the four interventions which will each be represented by dummy variables. Each intervention will be used in turn as the reference category to make all relevant comparisons.

##### 

**Predictors of cost** Participant characteristics will be used in a regression model to explain differences in baseline costs. We will test the hypothesised associations with both healthcare and societal costs, as well as using multivariable modelling of other possible predictors identified from univariate analyses. Subsequent regression models will be used to explain variations in follow-up costs, and these will also include clinical characteristics from preceding periods. Two types of regression model will be used. First, we will construct ordinary least squares models, with bootstrapping used to produce reliable 95% CIs around the regression coefficients. Second, we will construct generalised linear models with a log link and gamma distribution to account for the skewness that is likely in the costs data.

Independent variables will include demographic characteristics (such as age, gender and marital status), year of randomisation, clinical variables (such as fatigue score, disability, depression, anxiety) and benefits status (whether receiving benefits and whether benefits are in dispute).

##### 

**Cost-effectiveness analysis** Cost-effectiveness will be assessed by linking data on service cost differences and outcome (fatigue and physical disability) differences [77]. If any intervention has significantly lower costs and significantly better outcomes then it will be deemed to be more cost-effective. If costs are significantly higher and outcomes significantly better or if there is uncertainty in these findings (indicated by the CIs) then we will use the net benefit approach and cost-effectiveness acceptability curves to assess cost-effectiveness. Cost-effectiveness results will be plotted on a cost-effectiveness plane. This will involve producing estimates of cost and outcome differences from 1,000 bootstrapped re-samples of the original data. Such planes will be produced for each combination of two-way group comparisons. The plane will inform us as to the probability that an intervention has either (i) lower costs and better outcomes, (ii) lower costs and worse outcomes, (iii) higher costs and better outcomes or (iv) higher costs and worse outcomes than each comparator.

##### 

**Cost-utility analysis** This will be conducted in the same way as the cost-effectiveness analysis but will use quality adjusted life years (derived from the EQ-5D) as the outcome measure.

##### 

**Predictors of cost-effectiveness/cost-utility** The net-benefit approach allows multivariable analyses of economic data. This will enable us to identify predictors of cost-effectiveness and cost-utility. This will be done using regression models as described above. In particular we hypothesise that age and gender will predict cost-effectiveness and cost-utility.

##### 

**Baseline adjustment** The predictors of the cost regression model will be adjusted by the CSRI baseline outcome data.

##### 

**Model assumptions checks** Cost data are usually skewed and if this results in similarly skewed residuals then the standard linear model is inappropriate. The distribution of the regression residuals will be checked visually and if the distribution is non-normal we will use bootstrapping with 10,000 resamples to estimate 95% CIs around the cost differences (CIs will be based on the percentile or bias-corrected method depending on the level of bias observed in the model.) The assumption of independent residuals will be checked by bootstrapping at the therapist level.

##### 

**Other analyses supporting the primary analysis (including sensitivity analyses)** Sensitivity analyses will be carried out on two aspects of the analyses to assess the robustness of the findings. The effect of each of these alternative approaches on mean total societal costs at 12 months and subsequent cost-effectiveness calculations based on these costs will be explored in turn.

The main analyses will use an informal care unit cost based on the replacement method (where the cost of a homecare worker is used as a proxy for informal care). We will alternatively use a zero cost and a cost based on the national minimum wage for informal care. We will also conduct sensitivity analyses around the costs attached to lost employment.

The estimated costs of APT, GET and CBT will be increased and decreased by 50% to see how sensitive the costs, cost-effectiveness and cost-utility findings are to these variables.

#### **
*Subgroup analyses*
**

Exploratory sub-group analyses are planned to investigate whether intervention effects differ between those meeting and not meeting the CDC criteria or London criteria and between those with or without a depressive disorder at the point of randomisation.

#### **
*Software*
**

The data has been entered and checked during the course of the trial in a customised Microsoft Access [78] database. Once the database is locked, the data will be transferred into Stata [79]. It is anticipated that the analyses will be carried out primarily within Stata [79], although MLwiN [80] and other statistical packages may be used as necessary. The most up-to-date version available will be used in each case.

